### Intervention

2.3

The intervention will be preceded by a broad search in the literature to identify the topics to be included in the educational sessions and to substantiate the design of meetings with patients, as well as the methods indicated to encourage interaction between participants. The literature review included MEDLINE, LILACS, CINAHL, and COCHRANE databases. We considered studies published from 1st July 2007 to 31st January 2018. The intervention strategy was designed to adopt a patient-centered care approach following the Paulo Freire's theory.^[16,17]^ Freire is a Brazilian educator who has developed a theoretical framework based on problematization to promote education. He is widely renowned by his educational concepts that propose the principles of dialogue, autonomy, humanization, and emancipation. We elaborated the intervention using the principle of health empowerment ^[16,18]^ and we will apply techniques adapted to patients with low socioeconomic status and inadequate health literacy ^[19]^ (Fig. 1).

**Figure 1 F1:**
[figure not shown]
Intervention plan. AF = atrial fibrillation, TTR = time in therapeutic range.

The topics selected for the intervention sessions were: “knowing the medical condition and the anticoagulation indication”, “appropriate use of warfarin and other drugs taken by the patient”, “drug-drug and drug-food interaction?” and “risks and benefits from the treatment”.^[8,20]^

The intervention will be developed in groups of 12 participants at maximum. It will begin with a “culture circle”, defined as a learning method based on “generating words” that reflect the participants’ life experiences. The “generating words” will be identified by an immersion of the researcher in patient care process. Recognition of the context and the patients’ needs about the care process will be carried out. The educator will promote a debate to strongly motivate each group participant. Patients will be encouraged to share their life experiences and fears with other people who may have similar experiences. Thus, they will be able to develop a critical opinion out of their own background.^[16,17]^

Each group of 12 patients will participate in 4 face-to-face meetings, with intervals of approximately 30 days. As the topics will be repeated in each group, patients who miss a meeting will have other opportunities to attend the missing topic. Each meeting will be composed by a warm-up step, followed by the topic presentation and the learning construction. Participants will be invited to exchange experiences about warfarin therapy, to identify their main goals and obstacles, and to set future goals to be pursued. Each meeting is planned to last 1 hour, with a possible extension to 1 hour and a half, when necessary.

One clinical pharmacist trained on health education will conduct the intervention together with supervised Pharmacy undergraduates. Researchers will receive specific training by a senior researcher with experience in the methodology to develop skills in techniques to promote self-care and to stimulate patient empowerment. Pilot educational sessions will be offered to an independent group of patients with similar sociodemographic characteristics and a thrombosis history who are assisted at different week days of the intervention group at HC-UFMG. These patients will not be included in the study analyses. Researchers will not get involved in patient care during the study period, which will be under the responsibility of the AC professionals.

In-between meetings, each patient will receive a telephone call. On the first telephone call, the patients will be asked about their goal related to the treatment and what they have been doing to achieve that. On the second telephone call, they will be asked about warfarin adherence and about personal strategies to not miss warfarin doses. On the third and fourth telephone calls, the patients will be asked about the consumption of foods rich in vitamin K and about the use of other medications taken continuously. In this approach, a protocol will be used to ask questions and information will be registered on a standardized form. Patients will be constantly stimulated to take active participation in the intervention.

The pilot study will be conducted in March and April, 2019. The intervention will begin in April and May 2019 and it is planned to be concluded by September and October, 2019. Intervention will last approximately 5 months taking into account extra group sessions to replaced missing intervention meetings. Data collection will conclude by 12 months after the intervention. The study design is depicted in Figure 2.

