### Sample size

2.5

Sample size was calculated using diggle.linear.power function of longpower package in the software R 3.4.4 version.^[21]^ The TTR will be prospectively assessed, from T0 to T5. We considered an absolute increase of 6% in TTR with standard deviation of 7.5,^[22]^ 80% power, level of significance of 0.05 and at least 15% of variation in the slope coefficient between intervention and control groups. The calculated sample was 71 individuals for each group, and we planned to include 20% additional patients to account for a follow-up loss, resulting in 85 individuals allocated in each group. Also, we used composite symmetry autocorrelation structure with a correlation of 0.80 between the times of data collection.

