### Statistical analysis

2.9

TTR will be calculated by the Rosendaal method using a linear interpolation of INR results. TTR will be calculated at least 2 INR measurements. For participants who had INR intervals higher than 56 days, we used INR values to calculate TTR for the valid intervals (<56 days) and afterward we used the independent TTR values to calculate the final TTR by the arithmetic mean.^[33]^

Categorical variables will be expressed as frequency and percentage. Symmetric continuous variables will be expressed as means and standard deviation while asymmetric data will be expressed as median, first quartile, and third quartile.

To evaluate significance of each variable in the outcomes, univariate models will be adjusted using generalized estimation equation (GEE) with appropriate distribution for each outcome (normal or gamma distribution for TTR and binomial distribution for knowledge and adherence). Wald tests will be performed for each variable coefficient using an initial significance level of 0.20. All variables identified as initially significant will be added to a multivariate model and significance level will be set at 0.05. One final GEE multivariate model will be presented for each outcome including exclusively significant coefficients. Post hoc analysis will include comparisons of outcome means (or probabilities) at different time points. Statistical analysis will be performed in R version 3.4.4.

Patient refusal, death or other situations that would make it difficult for the patient to continue in the study will be registered and they will be considered as an intention to treat for analysis. Important protocol modifications will be reported to REBEC.

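### Patients are taught in about eight interactive groups in one arm only, but the sample size, and the GEE on its natural reading, allow only for correlation within a patient

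*Protocol article*

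**What the plan says.** Section 2.3 sets the delivery format: "The intervention will be developed in groups of 12 participants at maximum", and "Each group of 12 patients will participate in 4 face-to-face meetings, with intervals of approximately 30 days". The sessions open with a culture circle and go on through debate and shared experience. A missed session can be made up: "patients who miss a meeting will have other opportunities to attend the missing topic". One person leads: "One clinical pharmacist trained on health education will conduct the intervention together with supervised Pharmacy undergraduates". The control clinic gives usual care without groups.

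Section 2.5 bases the sample size on a slope comparison: "We considered an absolute increase of 6% in TTR with standard deviation of 7.5", with "80% power, level of significance of 0.05 and at least 15% of variation in the slope coefficient between intervention and control groups". The only correlation entered is 0.80, compound symmetric, between data collection times. The result is "The calculated sample was 71 individuals for each group", raised by 20% to 85.

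Section 2.9 states that "univariate models will be adjusted using generalized estimation equation (GEE) with appropriate distribution for each outcome". It names neither the clustering unit nor the education group.

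**The concern.** Members of one education group share meetings, discussion and peer influence, and interaction is the intended mechanism. Their changes in TTR, knowledge and adherence may therefore be more alike than those of patients in different groups. This can happen in the intervention arm only, so the design is partially nested.

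The sample size has no term for it. In the GEE, the natural clustering unit is the patient, because each patient is measured up to six times. A robust variance clustered on the patient protects against a wrong correlation structure within that patient. It does not protect against correlation between two patients of the same group. With a positive group ICC, the standard error of the arm comparison would be understated, the real type I error would exceed 5%, and the power would fall short of 80%.

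**Working it through.** **Inputs from the article.** Groups of at most 12 (2.3); 71 evaluable and 85 enrolled per arm, 80% power, alpha 0.05, SD 7.5, within-patient correlation 0.80, six times T0 to T5 (2.4, 2.5). **Assumptions.** Two-sided test; ICC of 0.01 to 0.10, on the scale of the slope or change over time.

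**The plan's own figures.** 71 × 1.2 = 85.2, so the 85 reproduces. The 71 does not. With times 0 to 5, the sum of squares of time is 17.5, and the variance of one patient's slope is 7.5² × (1 − 0.80) / 17.5 = 0.643. Then n = 2 × (1.960 + 0.842)² × 0.643 / d² ≈ 10.09 / d². A slope difference of 6/5 = 1.2 per visit gives about 7 per arm; 0.9 gives about 12; 0.18 (15% of 6, spread over five intervals) gives about 311; 0.15 gives about 449. The 80% at 71 per arm is therefore taken at face value below. The type I error figures do not depend on it.

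**Number of groups.** 85/12 = 7.1, so at least eight. With 71 evaluable patients in eight groups, m = 71/8 = 8.875.

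**Formulas.**
- Design effect, intervention arm only: DE = 1 + (m − 1) × ICC
- True SE divided by independence SE: r = √((DE + 1)/2)
- Real type I error of a nominal 5% test: 2 × (1 − Φ(1.960/r))
- Power of a correctly sized test: Φ(2.802/r − 1.960)

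| ICC | DE | r | SE increase | Type I error | Power |
|---|---|---|---|---|---|
| 0.01 | 1.079 | 1.019 | 2% | 5.5% | 78.5% |
| 0.02 | 1.157 | 1.039 | 4% | 5.9% | 77.0% |
| 0.05 | 1.394 | 1.094 | 9% | 7.3% | 72.6% |
| 0.10 | 1.788 | 1.181 | 18% | 9.7% | 66.0% |

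Example for ICC 0.05: DE = 1 + 7.875 × 0.05 = 1.394; r = √(2.394/2) = 1.094; 1.960/1.094 = 1.79, so 7.3%; 2.802/1.094 − 1.960 = 0.60, so 72.6%.

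**Sensitivity.** If all 85 per arm were analysed (m = 10.6), power would be 84.9, 83.3, 78.6 and 71.2% for the same four ICCs. The ICC at which it returns to 80% is (2 × 85/71 − 2)/(10.625 − 1) = 0.041.

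**Which group term matters.** T0 precedes the intervention, so a group effect can appear only as change after T0. A group intercept that is constant over time adds the same amount at every visit and contributes nothing to a slope. With 80 per arm in groups of 10, the SE of the slope difference is √(2 × 0.643/80) = 0.1268, whatever the variance of that intercept.

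**The case against.** - **No ICC is given.** A reader might infer that group members are correlated by design and that the standard error is certainly too small. The article does not establish that. One pharmacist leads the groups, the same topics are repeated in each, and individual telephone calls run between meetings. All of this could keep between-group variance low. An ICC near zero is possible, and then nothing is lost. This stands, and the point is conditional for that reason.
- **Make-up sessions mix the groups.** True, but to a limited extent. Section 2.2 counts two or more replacement sessions as loss to follow-up, so a patient counted as retained has made up at most one.
- **The clustering unit is not named.** A reader might say that the plan fixes the patient as the cluster. It does not; that is an inference from the repeated measures, and a full analysis plan could specify otherwise. The sample size is different: it is a finished calculation, and it has no group term.
- **The 20% allowance absorbs the loss.** Only up to an ICC of about 0.04, and only if nobody is lost. The allowance is meant for loss. A larger power deficit could be obtained by combining the group size from 85 enrolled (10.6) with the 80% power at 71 evaluable, but that mixes two sample sizes.
- **One clinic per arm is the larger problem.** Agreed. It is a separate matter of bias, whereas the point here concerns precision and would remain if the two clinics were identical.

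**Conclusion.** The point holds conditionally. The article describes delivery in about eight interactive groups in one arm, and a sample size that allows for correlation only between times within a patient. Its GEE, if clustered on the patient, has the same gap. Any positive group ICC would make the intervals too narrow and the 80% power an overstatement. The size cannot be settled from the article: over the assumed ICC range it runs from barely noticeable to material. The power figures rest on the stated 80%, which could not be rebuilt from the text, and on 71 evaluable patients per arm in eight equal groups.

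This is a secondary, inexpensive correction. The type I error figures should not be read as implying a valid 5% test once groups are modelled, because clinic and arm remain fully confounded.

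**What to change.** 1. Record each patient's original education group, and keep the patient in that group for analysis after any make-up session elsewhere.
2. In 2.9, name the clustering unit: education group in the intervention arm and the individual patient in the control arm, with a small-sample variance correction. Patients are nested in groups, so this also covers the repeated measures. It applies equally to the binomial models for knowledge and adherence.
3. If a mixed model is used instead, let the group random effect act on post-baseline change or slope, in the intervention arm only. A constant group intercept would leave the arm-by-time contrast unchanged.
4. Restate the power in 2.5 for a stated range of ICC, without enlarging the trial.

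The cost is one recorded variable and a somewhat wider interval. With about eight groups the ICC will be estimated imprecisely, which is why the small-sample correction is needed. None of this addresses the confounding of clinic with arm.

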**Figure 2 F2:**
[figure not shown]
Flow diagram. ACs = anticoagulation clinics, AF = atrial fibrillation, TTR = time in therapeutic range, INR = international normalized ratio.

### Outcomes

2.4

The primary outcome will be the oral anticoagulation control, assessed by TTR. We will consider as secondary outcomes knowledge on warfarin therapy and self-reported adherence to oral anticoagulation.

The outcomes will be compared intra and intergroups, using pre-defined time points to measure outcomes before and after the intervention. TTR and self-reported adherence to warfarin therapy will be measured 6 months before starting the intervention (T0), immediately after intervention completion (T1) and at 3 (T2), 6 (T3), 9 (T4) and 12 (T5) months after intervention completion. To prevent patients from exhaustion and considering that knowledge takes time to change, this variable will be measured at T0, T1, and T5 (Fig. 3).

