### Eligibility criteria

2.2

Patients assisted at the 2 ACs will be considered as potentially eligible for study participation. The inclusion criteria will be age ≥18 years, both sexes, follow-up in the ACs for at least 6 months, valvular or non-valvular AF as indication for warfarin use and TTR<60%. The exclusion criteria will be bedridden patients or limitation of locomotive disorders that compromises the attendance to office visits; total blindness or deafness; aphasia or other speech disorders that could hinder communication during study; dementia diagnosis reported in medical records; less than 2 INR values in the study period. Relatives or caregivers will be allowed to participate in the intervention, but they will not be assessed in this study. Follow-up loss will be considered as the absence in at least 2 intervention appointments or 2 or more intervention replacements.

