### Recruitment

2.6

Before recruitment, all patients assisted between August 2017 and September 2017 at the studied ACs (n = 1371) had their TTR calculated to identify those presenting TTR <60%. A new TTR calculation occurred between July and December 2018 to certify if patients with low TTR (<60%) identified in the first screening would continue to fulfill inclusion criteria. Thus, patients with persistently low TTR will be invited to participate in the study. To complete the sample, new patients with low TTR between July and December 2018 will be considered for inclusion in the study. Recruitment phase started in January and is expected to end by May. Patients’ invitation is planned to take place before or after scheduled appointments for monitoring oral anticoagulation.

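### The T0 baseline for TTR overlaps the July–December 2018 window used to select patients with low TTR, so within-group gains will include regression to the mean

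*Protocol article*

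**What the plan says.** **Baseline.** Section 2.4 (Outcomes) states that "TTR and self-reported adherence to warfarin therapy will be measured 6 months before starting the intervention (T0"). The abstract says only that T0 precedes the intervention. Section 2.3 (Intervention) gives the start: "The intervention will begin in April and May 2019".

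**Selection.** Section 2.2 (Eligibility criteria) requires TTR below 60%. Section 2.6 (Recruitment) describes two screens. In the first, "all patients assisted between August 2017 and September 2017 at the studied ACs (n = 1371) had their TTR calculated". The second covers July–December 2018.

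**Entry routes.** Under 2.6, "patients with persistently low TTR will be invited to participate in the study", meaning those low at both screens. To fill the sample, "new patients with low TTR between July and December 2018 will be considered for inclusion in the study".

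**Analysis.** Section 2.4 states: "The outcomes will be compared intra and intergroups". Each group is one clinic (2.1 Study setting). Section 2.9 (Statistical analysis) admits covariates at a univariate level of 0.20 and keeps only significant coefficients in the final model. It names no fixed term for entry route or screening TTR, and the data list in 2.4 does not name entry route.

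**The concern.** A patient's TTR in one window is part stable level and part chance. Selecting on a low value picks up patients whose chance component was low in that window. If the same INRs then form the baseline, the next measurement rises on average even when nothing has changed. The before/after comparison within the intervention group would count that rise as improvement.

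A second question concerns the two entry routes. Patients low in two windows regress less than patients low in one. If the clinics fill their samples with different shares of each route, the artefact would not cancel between groups, and clinic is the only thing that defines the groups.

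**Working it through.** The plan gives no figure for regression to the mean, so there is none to reproduce.

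**1. Dates.** April–May 2019 minus six months is October–November 2018.
- T0 as a point: wholly inside July–December 2018.
- T0 as a six-month look-back: a start on 1 April shares October–December (3 of 6 months); a start at the end of May shares about December only (1 of 6).

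The windows overlap on either reading.

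**2. Inputs.** From 2.5 (Sample size): SD 7.5, correlation ρ = 0.80 with compound symmetry, 85 per group, and a 6-point increase. Assumed: unselected clinic mean 60, normal TTR, no true change, and 7.5 taken as the SD of unselected TTR. A wider assumed case uses SD 20 and ρ = 0.5.

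**3. All patients low at the second screen, full overlap.** Expected rise = (1 − ρ) × SD × φ(k)/Φ(k), with k = (60 − mean)/SD. At mean 60, k = 0 and φ/Φ = 0.798.
- Plan's inputs: 0.2 × 7.5 × 0.798 = 1.20 points (0.64 at mean 55, 1.90 at mean 65).
- Wider case: 0.5 × 20 × 0.798 = 7.98 points.

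**4. Partial overlap.** If a fraction f of T0 is shared, the rise scales by about f.
- f = 1/2: 0.60 and 3.99 points.
- f = 1/6: 0.20 and 1.33 points.

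**5. What a within-group test would see** (plan's inputs, 85 patients). Variance of change = 2 × SD² × (1 − ρ) − [f(1 − ρ)]² × SD² × 2/π.
- f = 1: 22.5 − 1.43 = 21.07, SE = √(21.07/85) = 0.50. The rise is 2.4 SE, so p < 0.05 in about 67% of trials with no effect.
- f = 1/2: 22.5 − 0.36 = 22.14, SE = 0.51. The rise is 1.17 SE, about 21%.

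**6. By entry route, mean 60, full overlap.** Let P = 1/4 + arcsin(ρ)/(2π), the probability of being low in both windows. This is 0.398 at ρ = 0.80 and 0.333 at ρ = 0.5.
- Low in both: (1 − ρ) × SD × 0.1995/P = 0.75 and 5.98.
- Not low in 2017, low in 2018: (1 − ρ) × SD × 0.1995/(0.5 − P) = 2.92 and 11.97.
- Low in 2018, 2017 unknown: 1.20 and 7.98, as in step 3.

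**7. Between clinics.** If both have the same mix and TTR distribution, the difference is zero. Assume instead 50% by the top-up route in one clinic and 10% in the other, a gap of 0.4.
- Top-up patients simply low in one window: 0.4 × (1.20 − 0.75) = 0.18; 0.4 × (7.98 − 5.98) = 0.80.
- Top-up patients not low in 2017: 0.4 × (2.92 − 0.75) = 0.87; 0.4 × (11.97 − 5.98) = 2.40.

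Against the stated 6 points, that is about 3–13% and 15–40%. Half overlap halves these differences too.

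**The case against.** The design has real protection. The control clinic runs concurrently under the same TTR rule, with parallel data collection, and the sample size rests on a difference in slopes between groups. Regression common to both clinics cancels in that contrast. Requiring low TTR twice for the main route also reduces the artefact. TTR is calculated over an interval, so the look-back reading, with its smaller overlap, is at least as plausible as the point reading. The study flow charts are not shown and may define the window. All of this stands, and it limits the point.

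A reader might infer that the between-group result is biased. The documents do not support that. Nothing in them says the clinics differ in entry-route mix, and the 50% versus 10% split is an assumption. The wording on new patients may mean people who were not screened in 2017, rather than people screened then and found at 60% or above. The first meaning gives the smaller figures. A reader might also infer that the protocol will present within-group change alone as proof of benefit. It plans that comparison but does not say so.

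The concurrent control does not rescue the within-group comparison. It is planned, and its baseline is selected low on either reading of T0.

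**Conclusion.** The point holds for the within-group comparison. The protocol's own dates place T0 wholly or partly inside the selection window, so a rise in TTR without any effect is expected in both groups. With full overlap it is about 1.2 points on the plan's SD and correlation, nearer 0.75 if almost all patients were low twice, and about 8 points in the wider case. A look-back T0 brings these down to half or less. The sizes rest on an assumed clinic mean of 60, on normality, and on reading 7.5 as the spread of TTR before selection.

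For the between-group contrast, bias is possible but not shown. Under the assumed mix it would be 0.2–0.8 points or 0.9–2.4 points, depending on who the new patients are. The only usable yardstick is the stated 6 points, because section 2.5 gives neither the slope difference nor its time scale. The primary contrast is not invalidated, but the baseline definition is worth correcting because the remedy is cheap.

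**What to change.** - State the T0 calendar window. Compute T0 TTR only from INRs dated after 31 December 2018 and before the first session, over the same calendar window in both clinics. Use the July–December 2018 TTR for eligibility only.
- Record entry route (low at both screens, or July–December 2018 only) and say whether top-up patients were screened in 2017. Keep entry route and screening TTR in the TTR model whatever their p-values.
- Report the route mix by clinic.
- Base the conclusion on the group-by-time contrast and label within-group changes as descriptive.

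**Cost.** The INRs come from routine monitoring, so no new visits are needed. T0 shortens to about 3–4.5 months and becomes noisier. Section 2.9 needs at least two INRs and treats only intervals under 56 days as valid, so a few patients may lack a usable baseline. The plan should say how they are handled.
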